### Power and sample size

Assuming the proportion of those that are not frail (40%), mildly frail (60%) and moderately to severely frail (75%) will exhibit at least one cardiovascular event at 1 year. In order to detect these two comparisons (not frail, versus mildly frail & not frail versus moderately frail), using a chi-squared test with type-1 error = 0.025 and 80% power. We will need a minimum of 320 patients, approximately 120:120:80 for CFS 1–3, 4–5, 6–8 respectively.

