### Primary outcome

➢ Number of cardiovascular events (including hospital admissions due to cardiovascular cause) at 12 and 24 months in COPD patients living with frailty *vs* non-frail COPD patients.

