### Statistical analysis

We will aim to recruit a minimum of 320 patients: across a minimum of 3 sites.

This protocol and analysis plan will be drafted by a medical statistician fully blinded to the outcome data.

Data will be analysed for correlation between frailty and clinical outcomes. The primary analysis will be the number of cardiovascular events (time to event) at 12 and 24 months, adjusting for sex, age (18–64, 65–80, >80) and frailty at the time of recruitment, and other clinically relevant non-respiratory comorbidities. The number of events will be analysed using a zero-inflated Poisson regression to compare the rates between the three frailty groups. The rate with 95%CI will be presented alongside the p-value. Overdispersal will be assessed and if found to be present robust standard errors will be fitted.

The secondary analyses will assess the time to all-cause mortality, cardiovascular mortality, and mortality due to COPD that will be fitted to compare those classified as frail *vs* not frail visually using a Kaplan Meier plot. Data will be analysed using a multivariable Cox baseline proportional hazards regression, adjusting for covariates. The time to mortality will be calculated from the date of study entry to the end of follow up. The analyses will be presented as Odds Ratio (adjusted OR) with associated 95% confidence intervals and p-values. Subgroups analyses (age, sex, GOLD classes and grades, comorbidities) will be conducted to assess the grade of frailty. Stata version 18 (or later) will be used.

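### The zero-inflated Poisson count ratio is not the ratio of event numbers between frailty groups, and robust standard errors do not correct it under overdispersion

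*Protocol article*

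**What the plan says.** Under Primary outcome, the protocol article asks for "Number of cardiovascular events (including hospital admissions due to cardiovascular cause) at 12 and 24 months in COPD patients living with frailty", compared with patients who are not frail. That is a mean number of events per group.

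Under Statistical analysis, the model is fixed: "The number of events will be analysed using a zero-inflated Poisson regression to compare the rates between the three frailty groups". One result is promised: "The rate with 95%CI will be presented alongside the p-value". Overdispersion has one remedy: "Overdispersal will be assessed and if found to be present robust standard errors will be fitted". The section does not say which part of the model the rate comes from, whether frailty enters the inflation part, or whether the two parts are combined into a group mean.

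Under Power and sample size, the planned effect is on a different scale, the proportion of patients with any event: "Assuming the proportion of those that are not frail (40%), mildly frail (60%) and moderately to severely frail (75%) will exhibit at least one cardiovascular". The test is a chi-squared test, and "We will need a minimum of 320 patients, approximately 120:120:80 for CFS 1–3, 4–5, 6–8 respectively".

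**The concern.** A ZIP model splits the data into patients who can never have an event and patients whose counts follow a Poisson distribution. The usual output is a rate ratio for the second class alone. It equals the ratio of event numbers between frailty groups only if the never-event share is the same in every group. The planned effect concerns who has any event, which is the kind of contrast that the inflation part can absorb.

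The overdispersion rule adds a second problem. Robust errors work well with ordinary Poisson regression because its estimate of the mean stays consistent when the variance is wrong. A ZIP is a full-likelihood mixture. If the counts are overdispersed in another way, the estimates of both parts move, and a robust interval is then centred on the wrong value.

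At stake is the primary estimate. The reported ratio could understate, or in the extreme case miss, the difference in event numbers that the study sets out to measure.

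**Working it through.** **Inputs from the protocol article.** Proportions with any event at 1 year P = 0.40, 0.60, 0.75; group sizes 120, 120, 80; chi-squared test, type-1 error 0.025, power 80%.

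**Assumptions.** Event rate, never-event share and dispersion are not given. Two kinds of data are tried, both reproducing 40/60/75%. No covariates are included.

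**Step 1. The plan's own figure.** For 40% against 60%, two-sided:

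n per group = [2.241·√(2·0.5·0.5) + 0.842·√(0.4·0.6 + 0.6·0.4)]² / 0.20² = (1.585 + 0.583)² / 0.04 = 117.5, so 118.

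The stated 120 agrees. The 320 is sound for its own test.

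**Step 2. What the ZIP estimates.** With never-event share π and count mean λ:

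- P(no event) = π + (1 − π)e^(−λ)
- mean number of events = (1 − π)λ

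The ratio of event numbers against the not-frail group (subscript 0) is (1 − π)λ / [(1 − π₀)λ₀]. The count coefficient gives λ/λ₀.

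**Step 3. Frailty changes only who has events** (λ = 2 in every group). Then π = 1 − P/(1 − e^(−2)) = 0.537, 0.306, 0.133. The means are 0.925, 1.388 and 1.735, so the true ratios are 1.50 and 1.875 (0.60/0.40 and 0.75/0.40).

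- Frailty in both parts: λ = 2 throughout, ratios 1.00 and 1.00.
- Constant inflation: the large-sample maximum-likelihood values, with weights 120:120:80, are λ = 1.61, 2.03, 2.18 with π = 0.33. The ratios are 1.26 and 1.35.

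**Step 4. Negative binomial counts** with size k (variance = mean + mean²/k). The mean is μ = k[(1 − P)^(−1/k) − 1]. With frailty in both parts, the ZIP solves λ/(1 − e^(−λ)) = μ/P in each group.

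- k = 1: μ = 0.667, 1.5, 3.0; μ/P = 1.667, 2.5, 4.0; λ = 1.126, 2.232, 3.921.
- k = 0.5: μ = 0.889, 2.625, 7.5; μ/P = 2.222, 4.375, 10.0; λ = 1.885, 4.317, 10.00.

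With constant inflation, the large-sample values are λ = 0.977, 2.196, 3.943 (π = 0.298) for k = 1, and λ = 1.629, 4.313, 10.00 (π = 0.380) for k = 0.5.

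| Assumed data | True mean ratios | ZIP count ratio, inflation by group | ZIP count ratio, constant inflation |
|---|---|---|---|
| Effect only on who has events | 1.50 / 1.88 | 1.00 / 1.00 | 1.26 / 1.35 |
| Negative binomial, k = 1 | 2.25 / 4.50 | 1.98 / 3.48 | 2.25 / 4.03 |
| Negative binomial, k = 0.5 | 2.95 / 8.44 | 2.29 / 5.31 | 2.65 / 6.14 |

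Each pair is CFS 4–5 and then CFS 6–8, both against CFS 1–3.

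**Step 5. Robust errors.** In 1000 simulated trials per setting, the share of robust 95% intervals for the count ratio that contained the true mean ratio was:

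| k | Inflation by group | Constant inflation |
|---|---|---|
| 1 | 89% / 80% | 94% / 93% |
| 0.5 | 78% / 46% | 92% / 74% |

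**Step 6. Combining the two parts.** For k = 0.5 with frailty in both parts, (1 − π)λ = 0.472·1.885, 0.608·4.317 and 0.750·10.00, which return 0.889, 2.625 and 7.5. The ratio of combined means is therefore the true ratio.

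**The case against.** The strongest reply is that the article promises a rate and never names a count coefficient. A rate per frailty group could be the combined ZIP mean, which step 6 shows to be unbiased even under overdispersion when frailty is in the inflation part and there are no other covariates. Inflation covariates and post-estimation quantities could also sit in an analysis plan that is not shown. This stands as a limit: the bias belongs to the count coefficient, or to a model with constant inflation. It does not clear the plan. The article fixes the model, one reported rate and the overdispersion rule without specifying the combined mean, and the count ratio is the usual reading.

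It is also fair that the bias is not universal. With constant inflation and k = 1, the CFS 4–5 ratio is 2.25 against a true 2.25. The ratios of 1.00 need an effect that lies wholly in the never-event share, and an analyst who looked at the inflation part would see it there.

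Two further inferences are tempting and are not supported. A reader might infer from the planning proportions that zero inflation is unnecessary, but one proportion per group always fits a one-parameter Poisson and so is no evidence either way. A reader might also infer that patients who die early are treated as fully observed. The article states no exposure term, but its references to rates and to time to event are compatible with person-time, and an offset may be specified elsewhere.

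**Conclusion.** The point holds for the rate ratio that a ZIP reports by default. That ratio does not answer the question under Primary outcome, and the stated overdispersion rule does not repair it. Across the scenarios the count ratio ranges from no bias (2.25 for 2.25) to complete loss of the effect (1.00 for 1.88), with 5.31 for 8.44 under heavy dispersion. These sizes rest on assumed event rates and dispersion, on models without covariates, and on reporting the count coefficient or holding inflation constant.

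A reader might conclude that the study will miss its effect, or that 320 patients is a wrong figure. Neither follows. The documents do not show that frailty acts only through the never-event share, and the 320 reproduces for its chi-squared test. The defect lies in the quantity estimated and in the overdispersion rule.

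**What to change.** Name the marginal event rate ratio for each CFS group against CFS 1–3 as the primary estimate. Fit it by Poisson regression with a log link and robust standard errors, or by negative binomial regression, with follow-up time as offset. Keep the ZIP as a sensitivity analysis.

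If the ZIP stays primary, put frailty in both parts and report the ratio of combined means with a delta-method or bootstrap interval. The exact agreement in step 6 was shown without other covariates, so the planned adjustment would need the combined means to be checked.

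The cost is a short change to Statistical analysis, using standard Stata commands and data already planned for collection. The model is slightly less efficient if a ZIP is exactly true. The sample size section would also need a power statement for the rate ratio, with its assumed event rate and dispersion, because the present calculation covers only a difference in proportions.

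### The two frailty contrasts are sized at 0.025 each, but the primary comparison is to be reported with 95% intervals and no stated level, so the interval does not match the design

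*Protocol article*

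**What the plan says.** Protocol article, Power and sample size: the plan assumes that 40% of not-frail, 60% of mildly frail and 75% of moderately to severely frail patients have at least one cardiovascular event at 1 year. It names two contrasts, both against not frail: "In order to detect these two comparisons (not frail, versus mildly frail & not frail versus moderately frail". These are to be detected "using a chi-squared test with type-1 error = 0.025 and 80% power". The result is: "We will need a minimum of 320 patients, approximately 120:120:80 for CFS 1–3, 4–5, 6–8 respectively".

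Protocol article, Statistical analysis: "The number of events will be analysed using a zero-inflated Poisson regression to compare the rates between the three frailty groups". The next sentence fixes the output: "The rate with 95%CI will be presented alongside the p-value". The section gives no significance level for that p-value and no rule for multiple comparisons. The figure 0.025 appears only in the sample size section.

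**The concern.** Two contrasts at 0.025 each add up to 0.05, so the sample size section reads as an error rate split between them, although it does not say so. A 95% interval corresponds to a two-sided test at 0.05 for each contrast. For p between 0.025 and 0.05, say 0.03, the interval on the contrast excludes no difference while the p-value misses the design level. A reader of the published result would probably take the interval as showing an association.

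At stake is the protection that the split was meant to buy. For the contrast that drives the sample size, it raises the requirement from 97 to 118 per group, or 21 more in each of two groups. If the level is not carried into the analysis, that protection can be lost at the reporting stage, and the level could be chosen after the p-value is known.

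**Working it through.** **Inputs** (Power and sample size): event proportions 0.40, 0.60 and 0.75; type-1 error 0.025; power 80%; groups of 120, 120 and 80. No attrition allowance is stated and none is used. The interval level of 95% comes from Statistical analysis.

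**1. Reproduce the stated group size and settle sidedness.** For a chi-squared test of two proportions with equal groups and pooled variance under the null:

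n = [z_α √(2 p̄(1−p̄)) + z_β √(p₁(1−p₁) + p₂(1−p₂))]² / (p₂ − p₁)²

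With p₁ = 0.40, p₂ = 0.60, p̄ = 0.50 and z_β = 0.842, the two square roots are 0.7071 and 0.6928.

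- Two-sided 0.025 (z_α = 2.241): (1.585 + 0.583)² / 0.04 = 117.5, so 118 per group.
- One-sided 0.025, the same as two-sided 0.05 (z_α = 1.960): (1.386 + 0.583)² / 0.04 = 96.9, so 97 per group.

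With a continuity correction these become 128 and 107. The stated figure of approximately 120 fits uncorrected two-sided 0.025. Sidedness matters because a one-sided 0.025 test would agree with a two-sided 95% interval, and there would be no mismatch.

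**2. Power at the stated sizes.** For 40% against 60% with 120 per group:

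- at two-sided 0.025: Φ[(0.20√120 − 1.585)/0.6928] = Φ(0.875) = 80.9%
- at two-sided 0.05: Φ[(0.20√120 − 1.386)/0.6928] = Φ(1.162) = 87.7%

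The difference, 87.7 − 80.9 = 6.8 percentage points, is the chance under the planned effect that this contrast falls between 0.025 and 0.05, where the two levels disagree. For 40% against 75% at 120:80, power is 99.8% at two-sided 0.025, so disagreement there would be rare under the planned effect.

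**3. Chance of at least one false positive over the two contrasts.** Both contrasts use the not-frail group, so their test statistics are correlated:

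ρ = √[(120/240) × (80/200)] = √(0.5 × 0.4) = 0.447

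From the bivariate normal distribution with this correlation, when neither contrast has a true effect:

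| Level per contrast | Matching interval | At least one false positive |
|---|---|---|
| 0.025 | 97.5% | 4.7% (upper bound 2 × 0.025 = 5%) |
| 0.05 | 95% | 9.2% (1 − 0.95² = 9.75% if independent) |

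**4. Price of a matching interval.** 2.241 / 1.960 = 1.144, so a 97.5% interval is about 14% wider on the model scale.

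**5. Time points.** The sizing is for 1 year, while Primary outcome and Statistical analysis name both 12 and 24 months. Two contrasts at two time points make four tests. At 0.025 each, the upper bound is 4 × 0.025 = 0.10. The actual rate depends on the correlation between time points, which the documents do not give.

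**The case against.** The strongest objection is that no competing threshold exists. The analysis section states no rule that an interval excluding no difference counts as positive. A 95% interval is a customary reporting format, and the p-value beside it can be judged against 0.025, the only error level in the article. This stands. A reader might infer that the plan sets two contradictory thresholds, or that it commits itself to a 9% false-positive rate. The documents support neither, because they give no decision rule.

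Several narrower points also stand:

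- Two-sided is an inference. With an assumed 10% loss, which the article does not state, the one-sided figure with continuity correction would also come close: 107/0.9 ≈ 119. The chi-squared test and the uncorrected calculation still make two-sided the better reading.
- The interval is described as being on the rate. Intervals on each group's own rate would not test a contrast. An interval on the contrast is the more natural reading, since the sentence follows the comparison of groups and pairs the interval with a p-value.
- The analysis section does not name the pairwise contrasts, and a single p-value for three groups could be a global test. Aims and Primary outcome speak of frail against non-frail, which is one comparison. The point depends on the two contrasts for which the study was sized.
- The false-positive and power figures belong to unadjusted chi-squared tests, not to the adjusted count model.

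It can also be said that decision levels are usually left to a statistical analysis plan, which is not shown here. That would answer a complaint that a level is missing. It does not fully answer this point, because the article itself fixes both the 0.025 and the 95%, and the two do not correspond.

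**Conclusion.** The point holds as a mismatch between the level used to size the two contrasts and the interval chosen to report them. On the chi-squared sizing test at one time point, judging both contrasts from 95% intervals would give about a 9% chance of at least one false positive, against about 4.7% at 0.025 each. Under the planned 40% against 60%, roughly 7% of studies would land where the two levels disagree.

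This rests on 0.025 being two-sided and applying to each contrast, and on the reported interval being for the between-group contrast. The percentages would differ under the zero-inflated Poisson model, for which they were not computed. The mismatch between 0.025 and 95% does not depend on the model. Neither the sample size nor the point estimates are affected.

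**What to change.** In Statistical analysis, state that each of the two primary rate ratios against the not-frail group is judged at two-sided 0.025 and reported with a 97.5% confidence interval. Label any 95% interval shown for these contrasts as descriptive. In Power and sample size, write that the type-1 error is two-sided 0.025 per comparison.

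Claim an overall 0.05 only for one named primary time point. The sample size section is built on 1 year. Four tests at 0.025, over 12 and 24 months, would not secure it.

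The cost is a sentence or two in each section and primary intervals about 14% wider. No further patients or data are needed. The change should be made before outcome data are seen.

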### Aims

To assess whether frailty correlates with cardiovascular outcomes in patients diagnosed with COPD according to guidelines. The following research questions will be addressed:

How many cardiovascular events (including hospital admissions due to cardiovascular cause) at 12 and 24 months in COPD patients living with frailty *vs* non-frail COPD patients. Coronary artery disease (CAD), aortic disease, peripheral artery disease (PAD), cerebrovascular disease, deep vein thrombosis (DVT) and pulmonary embolism (PE), and arrhythmias were selected as cardiovascular events. The list of ICD-10 codes related to cardiovascular events of special interest for the study protocol is shown in **Table 1**.How many deaths due to cardiovascular cause at 12 and 24 months in COPD patients living with frailty vs non-frail COPD patients.How many deaths due to all-cause mortality at 12 and 24 months in COPD patients living with frailty *vs* non-frail COPD patients.How many deaths due to COPD at 12 and 24 months in COPD patients living with frailty *vs* non-frail COPD patients.Prevalence of frailty in COPD.

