### Secondary outcomes

➢ Long-term cardiovascular mortality at 12 and 24 months in COPD patients living with frailty *vs* non-frail COPD patients.➢ All-cause long-term mortality at 12 and 24 months in COPD patients living with frailty *vs* non-frail COPD patients.➢ Mortality due to COPD at 12 and 24 months in COPD patients living with frailty *vs* non-frail COPD patients.➢ Prevalence of frailty in COPD.

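### Kaplan-Meier curves for cardiovascular and COPD death overstate the absolute risk the aims ask about; cumulative incidence curves should replace them

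*Protocol article*

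**What the plan says.** The Statistical analysis section of the protocol article gives one method to three mortality endpoints: "The secondary analyses will assess the time to all-cause mortality, cardiovascular mortality, and mortality due to COPD". Frail patients are to be compared with those "not frail visually using a Kaplan Meier plot". The model follows: "Data will be analysed using a multivariable Cox baseline proportional hazards regression, adjusting for covariates". The only rule on the time scale is "The time to mortality will be calculated from the date of study entry to the end of follow up". The article does not say how a death from another cause is handled in the cardiovascular and COPD analyses, and it mentions neither competing events nor cumulative incidence.

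The quantities wanted are set out elsewhere. The Aims ask "How many deaths due to cardiovascular cause at 12 and 24 months in COPD patients living with frailty", compared with the non-frail, and likewise "How many deaths due to COPD at 12 and 24 months in COPD patients living with frailty". The Secondary outcomes section repeats the fixed horizons: "Long-term cardiovascular mortality at 12 and 24 months in COPD patients living with frailty".

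**The concern.** All-cause death has no competing event, so Kaplan-Meier suits it. Cardiovascular and COPD death do: a patient who dies of something else can no longer have the event. A Kaplan-Meier curve for one cause treats that patient as censored, as if still at risk after leaving view. One minus the curve then describes a setting in which nobody dies of anything else. The aims ask how many such deaths actually occur by 12 and 24 months, and that is a cumulative incidence.

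The overstatement grows with mortality from other causes. If that mortality is higher in the frail, their curve is pushed up more than the non-frail curve, and a reader comparing risks on the plot sees too wide a gap. At stake are the displayed absolute risks for two of the three mortality outcomes.

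**Working it through.** **No figure to reproduce.** The article states no mortality rate and no expected value for these curves. Its sample-size figures (320 patients, 120:120:80) concern cardiovascular events at 1 year. The group sizes are used below only for a standard error.

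**Inputs.**
- Horizons of 12 and 24 months: Aims and Secondary outcomes.
- Direction of overall mortality: the Introduction says that frailty can raise mortality in COPD. It gives no rates and no split by cause.
- Assumed: m, the 24-month all-cause mortality in a group, set at three levels from low to high; s, the share of deaths from the cause of interest, 30% in both groups; constant hazards.

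**Formulas.** The cumulative all-cause hazard is −ln(1−m), of which a fraction s belongs to the cause of interest.
- Cumulative incidence = s × m.
- One minus Kaplan-Meier, other deaths censored = 1 − (1−m)^s.

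Example, frail, m = 30%: cumulative incidence 0.3 × 0.30 = 9.00%; one minus Kaplan-Meier 1 − 0.70^0.3 = 10.15%. The excess is 1.15 points, or 12.8% of the true value.

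**Results at 24 months, s = 30%.**

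| All-cause mortality, non-frail/frail | Cumulative incidence | Difference | One minus KM | Difference | Relative excess, non-frail/frail |
|---|---|---|---|---|---|
| 5%/15% | 1.50%/4.50% | 3.00 | 1.53%/4.76% | 3.23 | 1.8%/5.7% |
| 10%/30% | 3.00%/9.00% | 6.00 | 3.11%/10.15% | 7.04 | 3.7%/12.8% |
| 20%/50% | 6.00%/15.00% | 9.00 | 6.48%/18.77% | 12.30 | 7.9%/25.2% |

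**At 12 months, same hazards.** The difference goes from 1.58 to 1.64 points, from 3.36 to 3.64, and from 5.62 to 6.58.

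**Wider range.** With s from 20% to 50%, equal in both groups, and 24-month mortality from 3%/10% to 20%/50%, the difference is inflated by about 0.1 to 3.7 points.

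**Where the contrast is not clearly inflated.** With 10% mortality and s = 30% in both groups, both curves rise to 3.11% and the difference stays at zero. With 10%/30% mortality and s of 50% in the non-frail but 95% in the frail, the difference moves only from 23.50 to 23.61 points and the ratio falls from 5.70 to 5.60. A 95% share cannot hold for cardiovascular and COPD death together.

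**Scale against sampling error.** At 10%/30%, with 120 non-frail and 200 frail patients, the standard error of the true difference is √(0.03×0.97/120 + 0.09×0.91/200) = 0.0255, or about 2.6 points. The excess is 7.04 − 6.00 = 1.04 points.

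**Sensitivity to the other-cause hazard.** Take annual hazards (cardiovascular, other) of 0.05 and 0.05 in the non-frail and 0.08 and 0.25 in the frail. One minus Kaplan-Meier at 24 months is 1 − exp(−0.10) = 9.5% and 1 − exp(−0.16) = 14.8%, a ratio of 1.55. Cumulative incidence is (0.05/0.10)(1 − exp(−0.20)) = 9.1% and (0.08/0.33)(1 − exp(−0.66)) = 11.7%, a ratio of 1.29. This is a steep case: frail all-cause mortality is 1 − exp(−0.66) = 48%. Lowering only the frail other-cause hazard to 0.10 gives a cumulative incidence of (0.08/0.18)(1 − exp(−0.36)) = 13.4%, and the ratios become 1.55 and 1.48.

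**The case against.** The strongest reply is that the plot is descriptive and the inference comes from the Cox model. This stands. A Cox model that censors other deaths validly estimates a cause-specific hazard ratio. A reader might infer that the planned effect estimates, intervals or p-values for frailty are biased; nothing in the article supports that. The harm is confined to two unadjusted secondary curves.

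A second reply is that the Follow up data section separately lists the number of deaths by cause at 12 and 24 months. With complete follow-up, simple proportions would answer the aims, and the article does not say that risks will be read off the curves. This lowers the stakes. It does not make the curve a correct display of the quantity asked for.

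A reader might also infer that the curves necessarily exaggerate the frailty contrast. The article does not establish this. The Introduction speaks of overall mortality, so higher other-cause mortality in the frail is plausible but not stated. The contrast also depends on the quantity meant: in the steep example the cause-specific hazard ratio is 0.08/0.05 = 1.60, close to the 1.55 from Kaplan-Meier. That figure misleads only when read as a ratio of absolute risks.

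Finally, censoring of other deaths is implied by a single-cause Kaplan-Meier curve and not written out, and an analysis plan that is not shown may say more. The article nevertheless names the estimator for these endpoints.

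**Conclusion.** The point holds for the cardiovascular and COPD mortality curves. If deaths from other causes are censored, as the named method implies, one minus Kaplan-Meier overstates the absolute risk at 12 and 24 months in any group where such deaths occur. The extra inflation in the frail is conditional on higher other-cause mortality there.

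The size rests on assumed rates. At low mortality it is a fraction of a point and would hardly be seen; at the highest mortality considered it is about 3 points on a true difference of 9. In the middle case it is smaller than one standard error, but it is systematic and more patients would not remove it. This is a modest, easily corrected fault in the display of secondary outcomes. The all-cause curve and the Cox cause-specific hazard ratios stand.

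**What to change.** In the Statistical analysis section:
- Restrict Kaplan-Meier to all-cause death.
- For cardiovascular death and COPD death, plot Aalen-Johansen cumulative incidence by frailty group, with death from any other cause as the competing event.
- Report cumulative incidence with confidence intervals at 12 and 24 months by frailty group.
- Label the Cox results for these two endpoints as cause-specific hazard ratios, and say that deaths from other causes are censored in that model. The section currently announces odds ratios, so the label has to change in any case.

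The cost is a few sentences and standard Stata routines. Deaths by cause are already collected and the planned time-to-event analyses already need their dates, so no new data are required. The displayed cause-specific risks will be slightly lower than under Kaplan-Meier.

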**Methods:**

This protocol describes a European prospective cohort study of community-based people, in a stable condition with diagnosis of COPD (as defined by GOLD guidelines) across hospitals in Italy and UK. Frailty prevalence will be assessed using the Clinical Frailty Scale. At 1- and 2-year follow up, primary outcome will be the impact of frailty on the number of cardiovascular events; secondary outcomes: the influence of frailty on cardiovascular mortality, all-cause mortality, and deaths due to COPD. For the primary outcome a zero-inflated Poisson regression will compare the number of cardiovascular events at 1 year. Secondary outcomes will be analysed using the time to mortality.

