## Materials and methods

### Study summary

**Table 2** provides the summary of the study information.

**Table 2 pone.0300945.t002:** Study summary.

Study Title	Influence of frailty on cardiovascular events and mortality in patients with COPD
Study Design	Observational
Study Participants	COPD outpatients
Planned Size of Sample	320
Follow up duration	24 months
Planned Study Period	24 months
Research Question/Aim(s)	To assess frailty and number of cardiovascular events in adult patients with COPD in stable condition. To correlate frailty with long-term cardiovascular mortality, all-cause mortality, and mortality due to COPD in patients with COPD.
	The prevalence of frailty in COPD will also be measured.

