### Follow up data (12 and 24 months)

➢ Number of cardiovascular events.➢ Number of deaths due to cardiovascular cause.➢ Number of all-cause deaths.➢ Number of deaths due to COPD.➢ Frailty score using the Clinical Frailty Scale (**Fig 2**).➢ Follow up spirometry.

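### The three mortality analyses use Cox regression but are to be reported as odds ratios instead of hazard ratios, and the time definition does not name death

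*Protocol article*

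**What the plan says.** In the protocol article, the second half of the section Statistical analysis deals with mortality. It sets the endpoints: "The secondary analyses will assess the time to all-cause mortality, cardiovascular mortality, and mortality due to COPD". Frail and non-frail patients are to be compared by Kaplan-Meier plot. The model follows: "Data will be analysed using a multivariable Cox baseline proportional hazards regression, adjusting for covariates". Next comes the time variable: "The time to mortality will be calculated from the date of study entry to the end of follow up". The effect measure is given last: "The analyses will be presented as Odds Ratio (adjusted OR) with associated 95% confidence intervals and p-values".

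Three other places bear on how to read these sentences:

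- For the primary analysis, a zero-inflated Poisson regression of the number of cardiovascular events, the same section gives a separate measure: "The rate with 95%CI will be presented alongside the p-value".
- The abstract, under Methods, confirms the type of endpoint: "Secondary outcomes will be analysed using the time to mortality".
- The study summary (Table 2) gives the length of follow-up: "Follow up duration 24 months".

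**The concern.** The model and the effect measure do not belong together. The exponentiated coefficient of a Cox model is a hazard ratio. An odds ratio comes from a model for a binary outcome at a fixed time, such as logistic regression, and the article plans none.

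Two things can go wrong. If the analyst runs the Cox model and follows the reporting sentence, hazard ratios are published under the wrong name, and readers and later meta-analyses will misread them. If the analyst takes the reporting sentence as the instruction, a logistic model replaces the planned one, and the choice between the two is left open until the data are in hand.

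The time sentence adds a smaller difficulty. It does not say that the interval stops at death, and it does not say how patients without the event are censored. If every patient were given the full interval to a common end of follow-up, the analysis would carry no information on when deaths occurred.

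**Working it through.** **Which analysis the odds-ratio sentence governs.** It stands at the end of the paragraph on mortality, after the Cox model. The primary analysis already has its own measure, a rate with its interval. The abstract describes the secondary outcomes as time-to-event. The article mentions neither a logistic model nor a hazard ratio. The sentence therefore applies to the Cox analyses of the three mortality outcomes.

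**The plan's own figure.** The plan gives no figure for mortality. Its only sample-size figure is 320, under Power and sample size, and it rests on cardiovascular-event proportions. For 40% against 60%, two-sided alpha 0.025 and 80% power:

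n per group = [2.2414 × √(2 × 0.5 × 0.5) + 0.8416 × √(0.4 × 0.6 + 0.6 × 0.4)]² / 0.2² = 117.5, rounded up to 118.

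With the stated 80 in the third group, 118 + 118 + 80 = 316, which agrees with the stated approximate 120:120:80. Nothing in this depends on the mortality analysis.

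**How far a hazard ratio and an odds ratio differ.** Let p0 be 24-month mortality in non-frail patients. Under proportional hazards, p1 = 1 − (1 − p0)^HR and OR = [p1/(1 − p1)] / [p0/(1 − p0)]. The values of p0 and HR below are assumptions, because the documents give none.

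| p0 | OR if HR = 1.5 | OR if HR = 2.0 | OR if HR = 3.0 |
|---|---|---|---|
| 5% | 1.52 | 2.05 | 3.16 |
| 10% | 1.54 | 2.11 | 3.35 |
| 20% | 1.59 | 2.25 | 3.81 |
| 30% | 1.65 | 2.43 | 4.47 |

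Example at p0 = 20% and HR = 2.0: 1 − p1 = 0.8² = 0.64, p1 = 0.36, OR = (0.36/0.64)/(0.20/0.80) = 0.5625/0.25 = 2.25.

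The label alone can also mislead. If that hazard ratio of 2.0 were printed as an odds ratio, a reader would compute odds of 0.25 × 2 = 0.50, hence a risk of 0.50/1.50 = 33.3%, where the model implies 36%.

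The table fits all-cause mortality directly. For cardiovascular or COPD death it also assumes no competing deaths.

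**What the literal time rule would do.** Suppose each patient, dead or alive, is given 24 months. All times are then tied. With Breslow's handling of ties, the Cox estimate solves d1/d0 = (n1 × HR)/n0, where d is deaths and n is patients in each group. This gives HR = (d1/n1)/(d0/n0), the risk ratio. At p0 = 20% and a true hazard ratio of 2.0, that is 0.36/0.20 = 1.80. A simulation under these assumptions (300 runs, 1,200 non-frail and 2,000 frail patients per run) returned 2.01 with actual death times and 1.81 with all times set to 24 months. The Kaplan-Meier curve would be a single step. This result holds only under the literal reading.

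**The case against.** On the effect measure, the best defence is that the secondary outcomes are worded as mortality at 12 and 24 months, and a fixed-time outcome would suit an odds ratio. That does not rescue the sentence: the model named is Cox, and both the statistical section and the abstract call the analysis time to mortality. It can also be said that, if the Cox model is run, the estimate is a hazard ratio whatever its label. That is true, and it means the likelier harm is misreading, not a biased estimate.

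On the time variable, the defence is stronger. A reader might infer that a patient who dies at month 3 is counted for 24 months, and so that the time variable is simply wrong. The documents do not support this. In ordinary cohort usage a patient's follow-up ends at death or last contact, and only that reading makes sense of a Kaplan-Meier plot and a Cox model of time to mortality. A condensed article may also leave a detailed censoring rule to the full plan. What stands is that the sentence, as written, names neither death nor censoring and should be made unambiguous.

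A reader might also infer that dates of death are not collected, because the follow-up list has entries such as "Number of all-cause deaths". That list is a summary of outcomes. The case report form is in the S1 File, which is not shown, so the inference cannot be drawn.

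**Conclusion.** The effect measure stated for the three secondary mortality outcomes does not match the stated model and is wrong as written. This rests on the text alone and needs no assumption. Under the assumed non-frail mortality of 5% to 30%, the gap between the two measures is small when deaths are few (2.05 against 2.0) and substantial when they are many (4.47 against 3.0).

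The time definition is ambiguous, not shown to be wrong. The attenuation from 2.0 to about 1.8 illustrates the literal reading and is not a prediction of what the study will do.

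The primary analysis and the sample size of 320 are untouched. The Discussion counts long-term cardiovascular mortality among the primary research questions, but the outcome sections list it as secondary. The point should be fixed; it does not put the study's main result at risk.

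**What to change.** In Statistical analysis, make two changes.

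1. Replace the odds ratio with the adjusted hazard ratio and its 95% confidence interval.
2. Reword the time sentence along these lines: *Time runs from study entry to the date of death; patients not known to have died are censored at the date last known alive or at 24 months, whichever is earlier. For cardiovascular and COPD mortality, deaths from other causes are censored at the date of death, so that the estimate is a cause-specific hazard ratio.*

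The last clause is needed because two of the three outcomes are cause-specific, and a rule written only for all-cause death would leave deaths from other causes undefined.

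The cost is two reworded sentences. No patients or visits are added, and the sample size does not change.
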